More than 1 unit of the same drug for the same time prescribed	Scanned once, then the number of tablets is manually adjusted	Every drug unit is scanned	Scanned once, then the number of tablets is manually adjusted	Scanned once; a pop-up appears asking for the other tablets to be scanned
Patient away or sleeping	Prescribed medication is placed at the patients’ bedside, registered as given, and checked at 2:00 AM	Medication not given and not registered; noted in memo field	Medication not given and not registered; noted in memo field	Not described in the instructions
One-half or one-quarter of a tablet prescribed	Tablet scanned, plus code “half” or “quarter” scanned on computer	Not described in the instructions	Tablet scanned, plus noted by nurse in memo field on the screen	Not described in the instructions
Instructions on screen for nurse from pharmacy or prescriber	On-screen memo field included (medication data level)	On-screen memo field included (patient data level)	On-screen memo field included (medication data level)	On-screen memo field included (medication data level)

We will collect the following potential risk factors for workarounds using a structured data collection form (Multimedia Appendix 1): nurses’ characteristics (experienced, trained, or student nurse; nurses’ satisfaction with BCMA), workload characteristics (number of nurses on the ward, number of patients served by that ward, number of medicines per round per patient, number of medicines for all patients per round per ward), BCMA system characteristics (time after implementation of BCMA system on that ward, bar code on medication unit dose), medication characteristics (Anatomical Therapeutic Chemical Classification System [ATC] code of the medication, drug administration route), and general characteristics (hospital type, ward type, time of ward round, patient age and sex). We will ask the supervisor of the ward for data on the nurses’ education and experience. We will extract the number of patients on the ward, the medication and ATC code, and the number of drugs to administer to each individual patient during the specific administration rounds from the CPOE system. We will ask the supervising hospital pharmacist for the other risk factors.

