### Data Collection

We will use disguised observation [30-34] to collect data. A total of 3 trained observers (undergraduate students, writing their master’s thesis) from the School of Pharmacy, University of Groningen and Utrecht University, the Netherlands, will observe the nurses while they give drugs to inpatients. To prevent nurses adjusting their behavior in the BCMA process while under observation, the observer will be introduced as being on the ward to monitor the performance of the medication distribution system on that ward. The observer will take part in several planned medication administration rounds on that ward and also observe unscheduled medication administrations. The observer will randomly pick a medication administration round with a minimum of 3 rounds every day and a weekly minimum of 18 rounds. During the different rounds, the observer will observe as many different nurses as possible. To prepare for the observation, the observer will study the standard operating procedures or the applicable drug administration procedures of the specific ward and the agreements on the BCMA process of that ward. In practice, the observer will accompany the nurse who administers the medication using the BCMA system and observe the administration of each dose of medication to the patient. The observer will record the nurses’ actions of giving drugs to the patients (according to the forms in Multimedia Appendix 1,Multimedia Appendix 2, and Multimedia Appendix 3). After each observed medication administration round, we will collect a (printed) computer output of the medication for that specific patient, day, and round from the hospital’s electronic patient records. Consequently, we will compare observation records with the prescribed medication on this computer output and with available standard operating procedures of the BCMA process for that specific ward, to identify workarounds and MAEs. We designed an Access database in which we will record the observation data and which we will link to each patient’s prescription and medication data.

If the observer becomes aware of a potentially serious error, the observer will intervene for ethical reasons, but the data will be included in the study.

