### Statistical Analysis

Data will be analyzed using IBM SPSS Statistics version 22 (IBM Corporation). We will analyze the potential association between workarounds and the occurrence of MAEs using univariate multilevel logistic regression, with the proportion of medication administrations with 1 or more errors as the dependent variable and the occurrence of workarounds as the independent variable. The nurse and the patient will be the levels in the multilevel analysis. We will analyze the occurrence of workarounds as a categorical variable, with the following categories: no workarounds (reference category), 1 workaround, 2 workarounds, and 3 or more workarounds. We will adjust for potential confounders by using multivariate multilevel logistic regression. The parameters in the multivariate multilevel logistic regression model will be hospital, ward type, day of the week, time schedule of medication administration rounds, ATC code, the number of drugs per patient per round, and the route of administration. We will report the adjusted odds ratio and 95% confidence interval. For the frequency and type of workarounds and MAEs, we will use descriptive statistics. Univariate and multivariate logistic regression will determine the association of the risk factors with the workarounds.

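### The adjusted MAE model leaves out nurse category, staffing and total ward-round medicine load, all collected as potential risk factors for workarounds, so the primary odds ratio is at risk of confounding by measured variables

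*Protocol article*

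**What the plan says.** The Statistical Analysis section names the terms of the adjusted multilevel logistic model for MAEs: "hospital, ward type, day of the week, time schedule of medication administration rounds, ATC code, the number of drugs per patient per round". One further term, the administration route, ends the list, which is worded as complete. On clustering it says: "The nurse and the patient will be the levels in the multilevel analysis".

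The Outcome Measures section lists the items gathered as potential risk factors for workarounds. They include nurse category ("experienced, trained, or student nurse") and four workload items. Three of these are "number of nurses on the ward, number of patients served by that ward, number of medicines per round per patient". The fourth is the total medicine count on the ward in a round. Statistical Analysis gives these risk factors one use, a secondary regression with workarounds as the outcome.

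Under Data Collection, the observations are made by a small team: "A total of 3 trained observers". The observer's record of a round is then compared with the prescriptions and the ward procedures to identify both workarounds and MAEs.

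**The concern.** A confounder here is something that makes a workaround more likely and also makes an error more likely by another route. The protocol itself proposes nurse category, staffing and ward load as candidates for the first link. For the second link, the Discussion says that many errors arise where staff meet the system, gives poor training or understanding as an example, and adds that such factors may lead to workarounds. Nurse category is the nearest variable collected, and it is absent from the model meant to remove confounding.

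If less experienced or overloaded nurses both work around the system more and err more, workarounds will look harmful even where they are not. That bias runs towards the study hypothesis. The study's message is that reducing workarounds could reduce MAEs, so part of the apparent benefit could belong to staffing or experience instead.

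**Working it through.** **1. Collected items against the adjusted MAE model.**

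| Item collected (Outcome Measures) | In the adjusted MAE model? |
|---|---|
| Nurse category | No |
| Nurses on the ward | No |
| Patients served by the ward | No |
| Medicines per patient per round | Yes |
| Medicines for all patients per round | No |

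One of the four workload items is in the model. Neither the staffing counts nor nurse category is.

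**2. Possible size, crude.** The plan gives no figure for this bias, so there is none to reproduce. Two inputs come from the Sample Size Calculation section: workaround prevalence W = 0.08 and an overall MAE rate of about M = 0.10. Two are assumptions: a share f = 0.30 of doses comes from nurses whose workaround and MAE rates are both r times those of the other nurses. Within each group workarounds have no effect. The exposure is simplified to any workaround against none, although the plan uses four categories.

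- Rates in the lower group: w = W / (f·r + 1 − f) and m = M / (f·r + 1 − f). The higher group has r·w and r·m.
- Joint probability: J = f·(r·w)(r·m) + (1 − f)·w·m.
- MAE rate with a workaround: J / W. Without: (M − J) / (1 − W).

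For r = 2, the divisor is 0.6 + 0.7 = 1.3:
- w = 0.0615 and r·w = 0.1231; m = 0.0769 and r·m = 0.1538.
- J = 0.3 × 0.1231 × 0.1538 + 0.7 × 0.0615 × 0.0769 = 0.0090.
- MAE rates are 11.24% and 9.89%, so OR = 1.15.

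For r = 2.5, the divisor is 0.75 + 0.7 = 1.45:
- w = 0.0552 and r·w = 0.1379; m = 0.0690 and r·m = 0.1724.
- J = 0.0098.
- MAE rates are 12.25% and 9.80%, so OR = 1.28.

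For r = 1.5 the same steps give OR = 1.05.

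**3. What the nurse level removes.** The figures above pool over nurses; the planned model does not. I simulated the same null scenarios with 6000 doses and a logistic model with a nurse random intercept. The number of nurses is not given, so it was varied (200 runs each; the patient level was left out).

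| Nurses | OR at r = 2 | OR at r = 2.5 |
|---|---|---|
| 40 | 1.02 | 1.04 |
| 100 | 1.08 | about 1.1 |
| 200 | 1.10 | 1.17 |
| 300 | 1.11 | 1.19 |

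The intercept removes most of the bias when each nurse contributes many doses (6000/40 = 150) and only about a third at r = 2.5 when each contributes few (6000/300 = 20). Data Collection asks observers to see as many different nurses as they can, which pushes towards the second case.

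**4. What it cannot remove.** Nurses on duty, patients served and total medicines can change from round to round for the same nurse. A term that is constant for each nurse does not represent that variation. The documents give nothing from which to size this part.

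**The case against.** The strongest reply is that the plan already does a good deal. It fits a nurse level and adjusts for hospital, ward type, day and round time, which may stand in for staffing patterns. It includes one direct workload item, and its limitations section concedes residual confounding and observer bias. Much of this stands. Workload is not wholly ignored, and the nurse level removes a real share of between-nurse bias. But calendar and ward terms are only proxies for staffing counts that have been collected. A general caveat about residual confounding does not explain why measured candidates were left out. Nor is this a detail left to another document, because the article fixes the list.

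A reader might infer more than the documents support, in four ways:

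- *That the odds ratio is confounded.* The text calls the items potential risk factors and gives no association between any of them and MAEs. Only a risk is shown.
- *That the crude odds ratios, or a false-positive rate computed from them, describe the planned analysis.* They ignore the nurse level and overstate its nurse-related bias.
- *That observer is an available covariate.* The text lists no such data field, and the forms are not shown. How observers were allocated is not stated; if they were split by hospital, the hospital term would absorb much of any difference between them.
- *That the within-nurse contrast should be the main result.* That changes the quantity estimated, whereas the stated aim is the association of workarounds with MAEs.

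**Conclusion.** The point holds as a risk of confounding by measured variables. Nurse category, staffing counts and total ward-round medicines are collected as candidate causes of the exposure, plausibly affect the outcome, and are missing from a closed adjustment list.

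The likely direction is towards the study hypothesis, if these factors raise workarounds and errors together. The size is unknown. Under the assumed scenarios the null odds ratio becomes 1.15 to 1.28 crude, and about 1.02 to 1.19 once a nurse intercept is fitted, before any round-level effect. This is modest beside the relative risk of 2 used for planning. To explain away a relative risk of 2 completely, a confounder would need risk ratios of about 2 + √(2 × 1) = 3.4 with both workarounds and MAEs. The omission could therefore distort a weak or moderate association more readily than it could create a strong one. It should be corrected, but it does not undermine the study.

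**What to change.** In the adjusted primary model, add as fixed effects:

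- nurse category (three levels);
- number of nurses and number of patients on the ward, or patients per nurse;
- total medicines for all patients per ward round.

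State whether observer identity is recorded for each round. If it is, add observer as a fixed effect, because the same observer's records identify both workarounds and MAEs, and differences in detection would move both together. A within-nurse contrast, obtained by also entering each nurse's workaround proportion, may be reported as a sensitivity analysis only.

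The cost is low. With linear terms for the counts, the additions use 2 + 1 + 1 + 1 = 5 degrees of freedom, plus 2 for three observers if available, against about 6000 × 0.10 = 600 expected erroneous administrations. Intervals will be slightly wider. The named risk factors need no new data, and since enrollment is reported as complete, the analysis is where this can still be addressed.

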**Figure 1 figure1:**
[figure not shown]
Flowchart of the bar code-assisted medication administration (BCMA) process in hospitals.

**Table 2 table2:** Classification of workarounds in the bar code-assisted medication administration process^a^.

Workaround type	Example workaround
Procedure related: standard operating procedure, or procedure unclear or unknown	Nothing scanned
Patient related: no patient wristband or patient not in the room	Bed scanned, or loose wristband scanned, patient unscanned
Medication related: medication not bar coded	Unscanned, unidentified medication given
Nurse related: nurse disturbed	Nurse forgets patient or gives medication twice
Computer or scanner related: computer or scanner down or broken	Signals or alerts unseen, unscanned medication given
Other workarounds	Medication scanned for multiple patients; half tablets scanned as full dose

^a^Derived from Koppel et al [26].

**Table 3 table3:** The most basic characterization of medication administration errors (MAEs)^a^.

MAE type	Example MAE
Omission	Drug prescribed, but not administered
Unordered drug administration	Drug administered, but not prescribed
Wrong dosage form	Drug dosage form administered to the patient deviating from prescribed dosage form: solution as an alternative to tablet
Wrong route of administration	Drug given by a wrong route of administration: oral liquid administered intravenously
Wrong administration technique	Drug administered using a wrong technique: intravenous push instead of intravenous infusion
Wrong dosage	Drug dosage too high or low: 20 mg instead of 20 μg
Wrong time of administration	Drug given at least 60 minutes too early or too late

^a^From van den Bemt et al [42].

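### The adjusted MAE model has no term for whether a dose is one whole unit, several units or part of a unit, a plausible dose-level confounder that the linked data could probably supply

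*Protocol article*

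**What the plan says.** In the Protocol article, Statistical Analysis, the adjusted model is given as a named list: "The parameters in the multivariate multilevel logistic regression model will be hospital, ward type, day of the week, time schedule of medication administration rounds", followed by "ATC code, the number of drugs per patient per round, and the route of administration". Nurse and patient are the levels. The result to be reported is the adjusted odds ratio with its 95% confidence interval.

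The risk-factor list under Outcome Measures gives the medication characteristics as "Anatomical Therapeutic Chemical Classification System [ATC] code of the medication, drug administration route". It has no item for units per dose or part tablets.

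Table 1 treats both kinds of dose as process features with their own rows:

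- "More than 1 unit of the same drug for the same time prescribed": hospital 2 scans every unit; hospitals 1 and 3 follow the rule "Scanned once, then the number of tablets is manually adjusted"; hospital 4 scans once and a pop-up then asks for the remaining tablets.
- "One-half or one-quarter of a tablet prescribed": hospital 1 scans an additional code, hospital 3 has the nurse write a memo, and the instructions of hospitals 2 and 4 are silent.

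Table 2 gives "half tablets scanned as full dose" as an example of a workaround. Table 3 defines the wrong-dosage MAE as "Drug dosage too high or low".

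**The concern.** A workaround is counted as a departure from the ward's protocol (Definitions and Classification). A dose with more prescribed steps, or different ones, offers more or different chances to depart. For part tablets the plan names such a departure outright. If the same doses are also more prone to a wrong amount, for instance through a miscounted or wrongly split tablet, dose-unit type is a common cause of exposure and outcome. It is set by the prescription before any workaround, so adjusting for it would not be over-adjustment.

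The listed covariates control it only in part. The number of drugs per round counts drugs, not units per drug. The same ATC code and route can be prescribed as half a tablet, one or two. The hospital term removes differences in procedure between hospitals, and the nurse and patient levels absorb some clustering. Neither removes differences between doses given by one nurse to one patient. At stake is the primary adjusted odds ratio, which could lie above 1 with no effect of workarounds.

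**Working it through.** The documents give no frequency of multi-unit or part-tablet doses and no error rate by dose type, so there is no figure of the plan to reproduce on this point. The sample size of 1500 per hospital does not depend on it. The check asks how large an odds ratio (OR) would appear with no true effect if dose-unit type were ignored.

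**Inputs from the Protocol article, Sample Size Calculation:** workaround prevalence 8%; overall MAE rate about 10%, quoted there from prior studies; planned relative risk 2.

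**Assumed inputs:** share q = 15% of doses that are multi-unit or part-unit; workaround rates w1 (these doses) and w0 (all others) of 24% vs 5.2% (stronger contrast) or 16% vs 6.6% (weaker contrast), both giving about 8% overall; MAE excess d on these doses.

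**Formulas.** With no association inside either dose type:

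- P(W) = q·w1 + (1−q)·w0
- m0 = 0.10 − q·d and m1 = m0 + d, which keeps the overall MAE rate at 10%
- P(MAE | W) = m0 + d·[q·w1 / P(W)]
- P(MAE | no W) = m0 + d·[q·(1−w1) / (1−P(W))]
- OR = ratio of the two odds

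**Worked case, stronger contrast, d = 5 points:**

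- P(W) = 0.15 × 0.24 + 0.85 × 0.052 = 0.0802
- Share of such doses: with a workaround 0.036/0.0802 = 0.449; without 0.114/0.9198 = 0.124
- m0 = 0.10 − 0.15 × 0.05 = 0.0925
- P(MAE | W) = 0.0925 + 0.05 × 0.449 = 0.1149
- P(MAE | no W) = 0.0925 + 0.05 × 0.124 = 0.0987
- OR = (0.1149/0.8851) / (0.0987/0.9013) = 1.19

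**All cases:**

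| Excess MAE on these doses | MAE rates, other vs these doses | OR, weaker contrast | OR, stronger contrast |
|---|---|---|---|
| 1 point | 9.85% vs 10.85% | 1.02 | 1.04 |
| 2 points | 9.70% vs 11.70% | 1.04 | 1.07 |
| 3 points | 9.55% vs 12.55% | 1.05 | 1.11 |
| 5 points | 9.25% vs 14.25% | 1.09 | 1.19 |
| 9.4 points | 8.6% vs 18% | 1.17 | – |
| 11.8 points | 8.2% vs 20% | – | 1.46 |

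**Wider grid,** shares of 5% to 30%, 8% workarounds and 10% MAEs overall, rates on these doses expressed as ratios to the others:

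- MAE ratio 1.5, workaround ratio 1.5 to 3: OR 1.01 to 1.14
- Both ratios 2 to 3: OR 1.05 to 1.42
- Both ratios 1.5 to 5: OR 1.01 to 2.12; every value of 1.4 or more needs both ratios to be at least 3

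For comparison, the planned relative risk of 2 at these overall rates means 0.10/1.08 = 9.26% vs 18.52%, an OR of (0.1852/0.8148) / (0.0926/0.9074) = 2.23.

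**The case against.** A confounder needs a link to the outcome as well as to the exposure, and the documents supply only the second. A reader might infer from Tables 1 to 3 together that units per dose demonstrably raises wrong-dosage errors. They do not say so: Table 3's one example is a milligram-for-microgram mix-up, which can happen with a single whole unit. Wrong dosage is also one of seven MAE types, so 11.8 extra points of any MAE on these doses is a heavy assumption.

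The workaround link is uneven too. In hospitals 1 and 3 the multi-unit rule is one scan plus a manual count, so no further scan exists to be skipped. In hospitals 2 and 4 it is unclear what would depart from a part-tablet procedure that is not described. The direction may therefore differ by hospital. A false rise across 1, 2 and 3 or more workarounds might also be inferred, but the plan does not say that each unit or step counts as a separate workaround.

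Finally, ATC code, route, hospital and patient level give partial control, and Strengths and Limitations concedes residual confounding.

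All of this stands as a limit on size and certainty. It does not remove the gap. The covariate list is closed, the plan's own tables single out these doses as handled differently, and a general remark on residual confounding does not answer for a variable that the linked records could probably supply.

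**Conclusion.** The point holds as a plausible, probably modest source of within-hospital confounding in the primary adjusted odds ratio. The workaround link is direct for part tablets (Table 2) and inferred for multi-unit doses (Table 1). The wrong-dosage link is inferred throughout.

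The likely bias is upward. At a 15% share and 1 to 5 points of excess MAEs, the spurious odds ratio is about 1.02 to 1.19. It reaches 1.4 or more only if both workarounds and MAEs are at least three times as frequent on these doses. The figures rest on assumed shares and rates and lean high, because they ignore the partial control from the listed covariates. Bias of this size would not by itself mimic the planned doubling, but it could inflate a weaker association. The documents support neither a claim that the primary result is seriously biased nor one that the dose-response pattern is spurious.

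**What to change.** From the prescription and medication data that the Access database links to each observation, derive a dose-unit category based on the prescribed dose:

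1. one whole unit
2. more than one unit
3. part of a unit
4. not applicable: liquids, injections and unordered drugs

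Where the number of units depends on the strength supplied, as it may with the bedside assortment cart in hospital 1, use the dispensed or ward-standard strength and state the rule before analysis. Unordered drugs are MAEs by definition. They should share level 4 rather than form a level of their own, which would predict the outcome perfectly.

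Add the category to the adjusted MAE model and to the risk-factor model. An interaction with hospital is worth examining, because the procedures differ. At minimum, report a sensitivity analysis restricted to single whole-unit doses. The covariate is the better choice, since restriction loses exposed doses disproportionately. Under the stronger contrast it would keep at most 0.85 × 6000 × 0.052 = 265 of 6000 × 0.0802 = 481 doses with a workaround.

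The cost is two or three degrees of freedom in about 6000 administrations, plus the derivation work. Enrollment is complete, so the variable must come from existing records. The article does not say whether the printed output shows units or only the dose, and this should be checked first.

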**Methods:**

This is a multicenter prospective study on internal medicine and surgical wards of 4 Dutch hospitals using BCMA systems to administer medication. We will include a total of 6000 individual drug administrations using direct observation to collect data.

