### Participants

The study will enroll patients admitted to the internal medicine and surgical wards of 4 Dutch hospitals in which a BCMA system is used to administer medication. To be eligible to participate in this study, a participant must meet the following criteria: be a hospitalized patient and receive medication on those nursing wards that are participating in this study. We will exclude patients younger than 18 years.

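### The risk-factor analysis of workarounds omits the multilevel structure used for the primary analysis, so intervals for nurse-, ward- and hospital-level factors will be too narrow as written

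*Protocol article*

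**What the plan says.** All quotes are from the protocol article.

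- **Primary association (Statistical Analysis).** The unadjusted analysis is done "using univariate multilevel logistic regression". For the adjusted one, "We will adjust for potential confounders by using multivariate multilevel logistic regression". The clustering is named: "The nurse and the patient will be the levels in the multilevel analysis". Hospital and ward type enter as covariates: "The parameters in the multivariate multilevel logistic regression model will be hospital, ward type, day of the week".
- **Determinants of workarounds (same paragraph, last sentence).** "Univariate and multivariate logistic regression will determine the association of the risk factors with the workarounds". No level, random effect or robust variance is named here, and no other section supplies one.
- **The factors (list following Table 1, under Outcome Measures).** Nurse grade ("experienced, trained, or student nurse") and satisfaction with the bar code system; staffing and patient numbers; time since the system was introduced on the ward; hospital type and ward type. The list also has dose- and patient-level items such as ATC code, route, age and sex.
- **The data.** "We will include a total of 6000 individual drug administrations" (abstract), from "internal medicine and surgical wards of 4 Dutch hospitals" (Participants). Under Data Collection, the observer accompanies a nurse and records every dose, so each nurse contributes many records.

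**The concern.** Two analyses of one dataset are described in one paragraph. The first is given a structure for repeated observations on the same nurse and patient; the second is not. The omission matters more in the second. A factor that is constant within a cluster carries only as much information as there are clusters, however many doses are observed in each. A single-level model counts every dose as a fresh observation of, say, nurse grade.

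Clustering of workarounds is to be expected here. Under Definitions and Classification, a workaround is a departure from the procedures of the particular ward, and under Setting those procedures differ between hospitals and, slightly, between wards.

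Identifying determinants is a declared secondary objective, and the abstract's conclusions say the information may help to focus work on reducing workarounds. Intervals that are too narrow would let chance differences between nurses, wards or 4 hospitals pass for determinants.

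**Working it through.** **Plan's own figures.** The article states no precision or power for the risk-factor analysis, so there is no figure to reproduce. Its sample size (1500 administrations per hospital, 4 × 1500 = 6000) is for the primary association, and this point does not depend on it.

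**Inputs from the article.** 6000 administrations; 4 hospitals; 1500 per hospital; workarounds in 8% of administrations (Sample Size Calculation), so 6000 × 0.08 = 480 expected.

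**Assumptions, because the article gives none.** 60, 120 or 240 nurses (6000/60 = 100, 50 or 25 administrations each); 8 to 16 wards (6000/8 = 750 to 6000/16 = 375 each); ICC over a range.

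**1. Nurse-level factor, by simulation.**
- Each nurse has a normal random intercept on the logit scale with SD s, where latent ICC = s²/(s² + π²/3).
- A factor with no effect is assigned to 30% of nurses.
- The single-level test is log OR / √(1/a + 1/b + 1/c + 1/d), with a to d the four cell counts, compared with ±1.96.

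| Latent ICC | s | 60 nurses | 120 nurses | 240 nurses |
|---|---|---|---|---|
| 0.02 | 0.26 | 11% | 8% | 6% |
| 0.07 | 0.50 | 24–25% | 16% | 10–12% |
| 0.20 | 0.91 | 47% | 33–34% | 22% |
| 0.33 | 1.27 | 59% | 46–47% | 33% |

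Entries are type I error at nominal 5%. Repeat runs agree to within about 2 percentage points.

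To judge the ICCs, start from odds of 0.08/0.92 = 0.087 and move one SD either way. At s = 0.26 the odds are 0.087 × e^±0.26, so nurses' rates run from 6.3% to 10.1%. At s = 0.91 they run from 3.4% to 17.8%.

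A similar simulation, with the factor held by half the nurses, 20 to 100 administrations per nurse and latent ICC 0.02 to 0.20, puts the correct standard error at 1.04 to 2.9 times the single-level one.

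**2. Ward- and hospital-level factors, by design effect.** DE = 1 + (m − 1) × ICC; interval width grows by √DE; actual coverage of a nominal 95% interval = 2Φ(1.96/√DE) − 1. This ICC is on the 0/1 scale, so it is not interchangeable with the latent ICC above. At ICC = 0.01:

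| Cluster | m | DE | √DE | Coverage |
|---|---|---|---|---|
| Ward, 16 wards | 375 | 1 + 374 × 0.01 = 4.74 | 2.2 | 63% |
| Ward, 8 wards | 750 | 1 + 749 × 0.01 = 8.49 | 2.9 | 50% |
| Hospital | 1500 | 1 + 1499 × 0.01 = 15.99 | 4.0 | 38% |

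The article's pilot error rates (2%, 4%, 5%, 20%) suggest that 0.01 is not extreme for hospitals. Their mean is 0.0775 and their variance 0.006825, and 0.006825/(0.0775 × 0.9225) = 0.095. That is only an indication: the hospitals and the outcome are different, and denominators are not given.

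**3. Factors that vary within nurses.** In a simulation of a null factor balanced within nurses, the single-level test rejected 3% to 5% of the time. Patient age and sex are fixed within a patient, but those clusters are small. With an assumed 3 doses per patient and round, DE = 1 + 2 × 0.20 = 1.4 even at ICC 0.20. It would be larger if the same patients are observed over many rounds.

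**The case against.** **The missing word may be an editorial slip.** The sentence closes a condensed paragraph that has already named the levels, and logistic regression does not by itself exclude random effects. That is possible. But the paragraph says multilevel for both primary models and not here, and nothing else in the article extends it. If it is a slip, the sentence still needs correcting.

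**Not every factor is fixed within a cluster.** This stands. ATC code, route, bar code on the unit dose and medicines per patient vary within a nurse. Staffing and patient numbers may change by shift or day; the article does not say they are constant on a ward. A reader might infer that the whole risk-factor analysis is invalid, but the listed factors do not support that.

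**The size rests on assumptions.** This also stands. With many nurses and an ICC near 0.02, the error for a nurse-level factor is close to nominal. A reader might conclude that all these intervals will be far too narrow; for nurse-level factors the article has no figures to establish that. For ward- and hospital-level factors a small ICC is enough.

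**It is an exploratory secondary analysis.** True. The article sets no significance threshold for it, and says only that the findings may help a focused approach. It does not commit to acting on them.

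**Conclusion.** The point holds for factors fixed, or nearly fixed, within a nurse, ward or hospital: nurse grade, satisfaction with the system, ward type, time since implementation and hospital type. As written, their intervals will be too narrow.

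For nurse-level factors the excess runs from slight to severe: type I error of about 6% to 11% at latent ICC 0.02, and 33% to 59% at 0.33, with 60 to 240 nurses. For ward- and hospital-level factors it is substantial even at ICC 0.01, with intervals that should be about 2 to 4 times as wide. The numbers of nurses and wards and the ICCs are assumptions throughout. Hospital type rests on 4 units whatever the model.

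A reader might carry the criticism over to the primary result. The article does not support that, because the workaround–error models are specified as multilevel. This should be fixed, but it does not threaten the main conclusion.

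**What to change.** Change the last sentence of Statistical Analysis so that the univariate and multivariable risk-factor models are multilevel logistic regressions with the nurse and patient levels already used for the primary model. For ward-level factors add a ward random intercept or a ward-clustered variance, since nurse and patient levels alone do not protect them. Enter hospital as a fixed effect. That absorbs hospital type, which should be reported descriptively across the 4 hospitals. State the numbers of nurses, patients and wards next to the results.

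The cost is one sentence. No new data are needed, multilevel logistic regression is already planned for the primary analysis, and the change can be made at the analysis stage. Intervals for cluster-level factors will widen, and with few wards those for ward-level factors may be too wide to be informative.
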